#### 3.3.3. Inference criteria.

We will compute posterior credible intervals for the precision and recall of the model [39]. Specifically, we will obtain the following statistics:

TP (number of true positives) =  True temper outburst that is predicted correctly.FP (number of false positives) =  Lack of temper outburst that is predicted as outburst.TN (number of true negatives) =  Lack of temper outburst that is predicted correctly.FN (number of false negatives) =  True temper outburst that is predicted as lack of outburst.

This allows us to perform Bayesian inference on the precision and recall as described in [32]. Using a prior lambda =  0.5 – the uninformative Jeffreys prior -- the posterior distributions of the precision and recall are as follows.

$Precision\sim Beta\left(TP+0.5.FP+0.5\right)$

$Recall\sim Beta\left(TP+0.5,FN+0.5\right)$

The posterior credible intervals can be obtained using the quantiles of these posterior distributions. Let QBeta(*q*, *a*, *b*) denote the quantile function for the Beta distribution with quantile *q* and shape parameters *a*, *b*. Hence, the 95% posterior credible interval for precision is

$Precision:\left[QBeta\left(0.025,TP+0.5.FP+0.5\right),QBeta\left(0.025,TP+0.5.FP+0.5\right)\right]$

$Recall:\left[QBeta\left(0.025,TP+0.5.FN+0.5\right),QBeta\left(0.025,TP+0.5.FN+0.5\right)\right]$

*Expected results.* Based on our preliminary results, where the regularized logistic regression model achieved a precision of 0.25 and recall of 0.69 for temper outbursts, we expect that the 95% posterior credible interval for the precision will contain a left endpoint greater than 0.1 and a right endpoint less than 0.4. We expect that the 95% posterior credible interval for recall will contain a left endpoint greater than 0.55 and a right endpoint less than 0.95.

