*Temper outbursts*	Overall	Morning	Afternoon	Evening
Mean (sd) [min, max] of participant-level frequencies of temper outbursts (*n* = 54)	0.10 (0.16) [0.0, 0.73]	0.10 (0.20) [0.0, 1.0]	0.08 (0.15) [0.0, 0.5]	0.11 (0.19) [0.0, 0.67]
Mean (sd) [min, max] of participant-level frequencies of temper outbursts for male participants (*n* = 34)	0.06 (0.09) [0.0, 0.33]	0.05 (0.12) [0.0, 0.57]	0.05 (0.11) [0.0, 0.5]	0.07 (0.12) [0.0, 0.57]
Mean (sd) [min, max] of participant-level frequencies of temper outbursts for female participants (*n* = 20)	0.17 (0.21) [0.0, 0.73]	0.19 (0.27) [0.0, 1.0]	0.14 (0.18) [0.0, 0.5]	0.18 (0.24) [0.0, 0.67]

**Table 3 pone.0289235.t003:** Outcome statistics (other than temper outbursts) for participants for preliminary data included in the analysis.

Variable	n (%) for total responses (out of 932 total)				
	1 (none of the time)	2	3	4	5 (the whole time)
*Irritability and related constructs (see table 2 for temper outbursts)*					
Irritable mood	516 (55%)	212 (23%)	147 (16%)	40 (4%)	17 (2%)
Frustration	482 (52%)	169 (18%)	139 (15%)	80 (9%)	62 (7%)
*Anxiety symptoms*					
Anxious affect	738 (79%)	78 (8%)	71 (8%)	31 (3%)	14 (2%)
Momentary anxiety	764 (82%)	83 (9%)	47 (5%)	26 (3%)	12 (1%)
*Momentary feeling state*					
Tired	309 (33%)	218 (23%)	163 (17%)	126 (13%)	116 (12%)
Happy	329 (35%)	163 (17%)	156 (16%)	149 (16%)	135 (14%)
Unhappy	656 (70%)	116 (12%)	86 (9%)	37 (4%)	37 (4%)
Giddy	681 (73%)	95 (10%)	80 (9%)	48 (5%)	28 (3%)
Hungry	424 (45%)	179 (19%)	164 (18%)	91 (10%)	71 (8%)
Mood changed	480 (52%)	184 (20%)	152 (16%)	58 (6%)	58 (6%)

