#### 3.2.3. Sample size.

In the confirmatory data set (to be completed by approximately 2027), we plan to collect 20 participants, with an expected total of 300.79 prompts. We determined this prospective sample size based on a power analysis with simulated data.

We simulated data based on a simulation ground truth logistic regression model with L2 penalization, and penalization constant tuned to produce data that would result in a cross-validated accuracy of around 0.40, matching what we saw in the real data. Then, by resampling without replacement participants from the training set, and drawing labels according to the predictions of the simulation ground truth model, we produced synthetic datasets with sample sizes ranging from 1 to 34 participants. For each target sample size, we drew 1000 synthetic data sets of that size, and we assessed the power in terms of the average proportion of coefficients with incorrectly estimated signs using regularized balanced logistic regression. Detailed results are presented in S1 Appendix.

Based on the results of the power analysis, there was a consensus that, when taking into account both the clinical and methodological considerations, the more conservative would be 25 participants, even though a case could be made to justify 15 participants. Our consensus decision is to take the average of these two extremes, and therefore our new plan is to stop collecting participants for this analysis once we have collected 20 participants, which results in around 300.79 prompts on average and has a 31% average sign error for estimating coefficients (Table in S1 Appendix). For this number of prompts, assuming the same proportion of prompts will contain outbursts as in the exploratory sample (10%), we expect to see 30.08 temper outbursts on average.

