### 3.3. Statistical models

#### 3.3.1. Data.

The full list of selected variables is as follows

Response variable: Temper outburst (binary)

Predictor variables:

non-time-varying:Demographic variables: age and self-reported sex assigned at birth.time-varying:Indicator variables from previous time point: giddy, tired, worried, happy, grouchy, angry, frustrated, worried, unhappy, change in mood.Time of day and day of week. See section 2.2.1, “Measured Variables” for details.

While we used data-splitting for model development in the analysis of the preliminary data, in the confirmatory dataset we will use the entire confirmatory dataset as a test set to evaluate the logistic regression classifier we have already developed.

**Transformations.** The day of week will be extracted from the timestamp of the raw data.

Recall that the data will be collected for 7 days, 3 times a day per observation period, with some participants completing multiple observation periods (details in sampling plan). The time of day will be obtained from the column number of the raw data (as columns 1-21 are the 21 consecutive EMA prompt periods, with morning, afternoon, and evening for each of 7 days). The participant’s age will be rounded to integer values.

All predictors will be rescaled to lie between 0 and 1 using min-max scaling. Observations with missing entries will be excluded from the analysis. Since we do not use observations with partial entries, we will report the missing cases on an observation-by-observation basis rather than a variable-by-variable basis.

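### The confirmatory credible intervals for precision and recall pool prompts as if independent, although outbursts cluster within the 20 youths, so the intervals are too narrow, more clearly for precision than for recall

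*Protocol article*

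**What the plan says.** Section 3.3.3 introduces its formulas by saying that "the posterior distributions of the precision and recall are as follows". It adds 0.5 to each pooled count ("the uninformative Jeffreys prior") and gives precision a Beta(TP+0.5, FP+0.5) posterior and recall a Beta(TP+0.5, FN+0.5) posterior. Quantiles of these distributions form the 95% intervals. Section 3.3.1 makes the whole confirmatory dataset the test set, so the counts run over every prompt of every youth. No participant term, resampling of participants or effective sample size appears.

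On sample size, section 3.2.3 says "we plan to collect 20 participants, with an expected total of 300.79 prompts" and, "assuming the same proportion of prompts will contain outbursts as in the exploratory sample (10%), we expect to see 30.08 temper outbursts on average". The anticipated performance in section 3.3.3 is that "the regularized logistic regression model achieved a precision of 0.25 and recall of 0.69 for temper outbursts".

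On clustering, Table 2 gives the participant-level outburst frequency as mean, SD and range: "0.10 (0.16) [0.0, 0.73". Section 3.3.1 also describes the data as collected three times a day for 7 days, "with some participants completing multiple observation periods (details in sampling plan".

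**The concern.** A Beta posterior on pooled counts is right only if the classified prompts are exchangeable, independent draws. Here they are repeated measures on a few youths. Age and sex enter the classifier as constants within a youth, and some youths report many outbursts while others report none. Hits, misses and false alarms will therefore tend to come in runs from the same youths.

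The article's own reasoning makes the youth the sampling unit. Section 1 chooses a population-level model so that it can serve families without individual training data. Section 2.1.2 splits the preliminary data by whole participants to get an unbiased view of performance. The confirmatory intervals drop that principle.

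These intervals are the only confirmatory inference. They are what the expected-results statement in section 3.3.3 is judged against, and they feed the second and third diagnostic triggers in section 3.3.4 (upper bound below the preliminary value; width above 0.5). If they are too narrow, the study will claim more certainty about new patients than 20 youths can give.

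**Working it through.** **1. Reproduce the plan's figures.** Expected outbursts: 300.79 × 0.10 = 30.08, as stated. Prompts per youth: 300.79 / 20 = 15.04. Table 4 follows from TP 9, FN 4, FP 27, TN 127: precision 9/36 = 0.25, recall 9/13 = 0.69.

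**2. Planned intervals at the expected counts.** TP = 30.08 × 0.69 = 20.8; FN = 9.3; flagged prompts = 20.8 / 0.25 = 83.0; FP = 62.3. I use the 0.025 and 0.975 quantiles, although the printed formulas repeat 0.025 at both ends (a separate point).
- Precision: 0.166 to 0.351, width 0.18.
- Recall: 0.513 to 0.832, width 0.32.

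**3. Is independence compatible with Table 2?** The preliminary data have 932 / 54 = 17.26 prompts per youth.
- SD of youth frequencies under independence: √(0.10 × 0.90 / 17.26) = 0.072. Table 2 gives 0.16.
- Between-youth variance: 0.16² − (0.09 − 0.16²) / (17.26 − 1) = 0.0216.
- Outburst ICC: 0.0216 / 0.09 = 0.24.

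**4. Approximate widening.** Use the design effect 1 + (m* − 1) × ICC, where m* is the size-weighted number of relevant prompts per youth, and divide the counts by it.
- Recall: the relevant prompts are outbursts. Mean per youth 15.04 × 0.10 = 1.504; variance 15.04 × 0.09 × (1 + 14.04 × 0.24) = 5.92; m* = (5.92 + 1.504²) / 1.504 = 5.44.
- Precision: the relevant prompts are flags, on average 83.0 / 20 = 4.15 per youth. The clustering of flags is not reported. Assuming a flag ICC of 0.10, 0.24 or 0.40 gives m* of 5.9, 7.3 or 8.9.

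The ICC of correct classification is not in the article either. The table takes m* = 5.44 for recall and 7.3 for precision.

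| Assumed ICC of correct classification | Precision | Width ratio | Recall | Width ratio |
|---|---|---|---|---|
| 0 (plan) | 0.17 to 0.35 | 1.0 | 0.51 to 0.83 | 1.0 |
| 0.05 | 0.16 to 0.37 | 1.15 | 0.49 to 0.84 | 1.11 |
| 0.24 | 0.13 to 0.41 | 1.59 | 0.44 to 0.88 | 1.44 |
| 0.50 | 0.10 to 0.46 | 2.04 | 0.37 to 0.91 | 1.79 |

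**5. Simulated coverage.** The set-up was 20 youths × 15 prompts, with a classifier score that is partly constant within a youth and a logistic outburst model with a further youth effect. It was calibrated to prevalence 0.10, precision 0.25 and recall 0.69, with 6,000 replicates per row. Coverage is that of the nominal 95% pooled Beta interval.

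| Share of score variance between youths | SD of extra youth effect (logit) | SD of youth frequencies | Precision | Recall |
|---|---|---|---|---|
| 0 | 0 | 0.077 | 94.7% | 95.2% |
| 0.5 | 0 | 0.108 | 92.8% | 89.0% |
| 0.3 | 1.0 | 0.121 | 85.9% | 89.4% |
| 0.3 | 1.5 | 0.143 | 80.2% | 87.9% |
| 0.5 | 1.5 | 0.152 | 75.4% | 82.4% |
| 0.7 | 1.5 | 0.167 | 69.3% | 77.0% |

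The first row checks the code. Other set-ups calibrated to the same figures, with a youth SD near 0.155, gave 72-77% for precision and 81-90% for recall.

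**The case against.** The strongest reply concerns size, not direction. Four parts of it stand.

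- **Design effect for all prompts.** A reader might take the outburst ICC of 0.24 with 15 prompts per youth, obtain a design effect of about 4.4, and conclude that 300.79 prompts are worth only about 69. That figure describes the outburst rate. Recall rests on about 30 outbursts and precision on about 83 flags, both with fewer relevant prompts per youth, so 4.4 and 69 do not carry over to these intervals.
- **Recall.** A reader might infer that both intervals are far too narrow. For recall the shortfall depends on how much of the classifier score varies between rather than within youths, which is not reported. If that share is modest, recall coverage stays in the high 80s even with clustering like Table 2. Precision suffers more consistently.
- **Multiple observation periods.** Section 3.3.1 mentions them, but the preliminary counts fit one period per youth (57 × 21 = 1197; 54 × 21 = 1134). They are a reason to define the cluster with care. They are not evidence of a larger effect.
- **Consequences.** No test or go/no-go decision hangs on the intervals, and the triggers start only exploratory diagnostics. At an ICC of 0.24 the recall width is about 0.44, still below the 0.5 trigger; it reaches 0.53 only at an ICC of 0.50. The expected recall lower bound above 0.55 already fails at the expected counts under independence (0.51), so clustering does not cause that failure.

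The reply that a fuller analysis plan might deal with clustering does not stand. The article prints the posterior formulas, and those formulas fix the independence assumption. The check for unusual participants in section 3.3.4 runs only if triggered and leaves the intervals unchanged.

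**Conclusion.** The point holds. The formulas in section 3.3.3 assume independence that Table 2 contradicts, and the resulting intervals are too narrow for a claim about new youths. With clustering near Table 2, nominal 95% coverage is roughly 70-80% for precision and 77-90% for recall; with milder clustering it is about 90% for both.

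The direction is firm. The size rests on two assumptions: that the confirmatory youths cluster as the preliminary ones did, and a range for the unreported within-youth correlation of correct classification. The documents do not support a single figure for the shortfall, nor an equal shortfall for the two measures.

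**What to change.** Amend section 3.3.3 before the confirmatory data are analysed, so that the primary intervals account for clustering by participant. Two suitable routes are:
- resampling whole participants, with all observation periods of a youth kept together; or
- a hierarchical or beta-binomial model that reports marginal precision and recall.

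Use the same intervals for the second and third diagnostic triggers in section 3.3.4. Keep the pooled Beta interval as a secondary display, labelled as assuming independent prompts.

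The choice of method should be the authors'. A fixed rule of participants minus one degrees of freedom is best avoided: with clustering like Table 2, about half of the youths (54% under a beta-binomial model) would report no outburst and so add nothing to recall.

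The cost is a short text change and a few lines of code, with no new data. The reported intervals become less favourable, about 1.4 to 1.6 times wider at an assumed ICC of 0.24. With about 20 clusters any such method is approximate, and the text should say so.

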#### 2.4.2. Logistic regression.

We determined the optimal number of time lags (1, 2, or 3) to use for logistic regression. The AUC for lag-1 was 0.73, the AUC of lag-2 was 0.78, and the AUC of lag-3 was 0.77. Hence, we selected lag-2 for regularized logistic regression. Detailed results of this analysis are included in S2 Appendix.

The best regularization scheme for logistic regression, as determined using 40-fold cross-validation within the training set, was L2 regularization with C = 0.01. In table 4, we present the model performance for regularized logistic regression, applied to the test examples.

**Table 4 pone.0289235.t004:** Prediction performance of temper outbursts for DMDD, sub-threshold DMDD, and ODD patients in held-out test examples of existing dataset, using regularized logistic regression.

	Precision	Recall	F1-score	Support
No outburst	0.97	0.82	0.89	154
Temper outburst	0.25	0.69	0.37	13

Precision, also called positive predictive value, is defined as the fraction of positive predictions that were true positives (the fraction of times where a temper outburst was endorsed out of the times that the model predicted a temper outburst). Recall, also called sensitivity, is defined as the fraction of positive examples that were predicted to be positive (the fraction of times where the model predicted a temper outburst out of the times in which a temper outburst was endorsed). F1-score is the harmonic mean of precision and recall, given by the formula F1 =  2 *  (precision *  recall)/ (precision +  recall). Support is the total number of test set observations in each category.

Table 5 presents the model weights for logistic regression, as well as Bayesian 95% credible intervals for the variables. We use the Pymc package [35] to implement the Bayesian inference, with N(0,400) prior for the intercept and N(0,0.01) prior (with sigma^2 = 0.01 chosen to match the selected hyperparameter C = 0.01) for each of the non-intercept beta coefficients. For MCMC, we used the NUTS sampler [36] with 10,000 draws and an acceptance target of 0.99.

**Table 5 pone.0289235.t005:** Model weights and intercept for L2-regularized logistic regression, and 95% credible intervals from Bayesian regression.

Variable (lag)	Coefficient	Bayesian 95% credible interval	Variable (lag)	Coefficient	Bayesian 95% credible interval
happy (1)	-0.20	[-0.26, 0.12]	happy (2)	-0.08	[-0.21, 0.18]
unhappy (1)	0.10	[-0.11, 0.27]	unhappy (2)	0.12	[-0.11, 0.27]

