#### 3.3.4. Exploratory analyses.

We include two main categories of exploratory analysis in this protocol. First is a post-hoc analysis of the performance of individualized prediction models. Second is an optional set of diagnostic analyses to be performed only if the result of the confirmatory analysis deviates from the preliminary analysis by a pre-defined margin.

##### 
Individualized prediction.

Individualized prediction involves taking the model trained on all participant data in the training set and then “fine-tuning” the model by optimizing for a few iterations on the data from an individual participant in the test set. Technically, this is accomplished by using the “warm-start” argument in the scikit-learn logistic regression class, combined with a low number of maximum iterations. The model individualized this way will then be compared to the original model in terms of performance on unseen data from that participant. This reflects a use case where an existing model would be adapted to a new participant using data collected at the beginning of a trial, and then used to generate predictions from that point onwards.

##### 
Diagnostic analyses.

There are several outcomes of the main analysis that would warrant further diagnostic analyses of the data. We are including these potential analyses in this section, since it is customary for a pre-registration to include planned exploratory analyses.

These are the scenarios which would trigger our diagnostic analyses.

1)If the AUC of the classifier on the confirmatory dataset differs from the AUC of the classifier on the preliminary dataset by more than 0.05.2)If the upper bound of the posterior credible interval for any of the following variables is less than the nominal value on the preliminary dataset. The variables are: precision for outburst, precision for non-outburst, recall for outburst, recall for non-outburst.3)If the width of the posterior credible interval for any of the variables listed in (2) above exceeds 0.5.

The diagnostic analyses include:

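### Both endpoints of the 95% credible intervals for precision and recall are set at the 0.025 quantile, so each interval is a single point

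*Protocol article*

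**What the plan says.** Section 3.3.3 (Inference criteria) gives Beta posteriors for precision and recall under "the uninformative Jeffreys prior", with 0.5 added to each count. It lets QBeta(q, a, b) "denote the quantile function for the Beta distribution with quantile" q and shape parameters a and b. It then introduces the result with "Hence, the 95% posterior credible interval for precision is" and prints these endpoints:

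- Precision: "QBeta\left(0.025,TP+0.5.FP+0.5\right),QBeta\left(0.025,TP+0.5.FP+0.5"
- Recall: "QBeta\left(0.025,TP+0.5.FN+0.5\right),QBeta\left(0.025,TP+0.5.FN+0.5"

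The same section sets out expected results, on the ground that the model "achieved a precision of 0.25 and recall of 0.69 for temper outbursts" in the preliminary data. The precision interval is expected to lie between 0.1 and 0.4, and the recall interval between 0.55 and 0.95.

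Section 3.3.4 (Exploratory analyses) uses the intervals again, for precision and recall of both outbursts and non-outbursts. Trigger 2 reads "If the upper bound of the posterior credible interval for any of the following variables is less than the nominal value" from the preliminary data. Trigger 3 applies when an interval is wider than 0.5.

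**The concern.** The first argument of QBeta is defined as the quantile, and it is 0.025 at both ends of both intervals. The value 0.975 appears nowhere in the article. Read as written, the formula contradicts three other statements in the document: the 95% level, the expected results with their separate left and right endpoints, and the triggers that need an upper bound and a width.

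These intervals are the only inference criteria set for the confirmatory sample. Section 1.1 says that the trained classifier is pre-registered so that specific hypotheses about its performance can be tested. A registered formula that cannot give the stated interval undermines that purpose, and correcting it after the data are seen would be a departure from the registered text.

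**Working it through.** **Inputs**

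- Table 4 (section 2.4.2), outburst row: "Temper outburst 0.25 0.69 0.37 13", that is precision 0.25, recall 0.69, F1 0.37 and 13 outbursts. Non-outburst row: precision 0.97, recall 0.82, 154 observations.
- Section 3.2.3: 300.79 prompts expected, 10% with outbursts, so 30.08 outbursts.
- Section 3.3.3: shapes TP+0.5 and FP+0.5 for precision, TP+0.5 and FN+0.5 for recall.

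**Step 1. Preliminary counts.** The only whole-number counts that match both rows of Table 4 are TP = 9, FP = 27, TN = 127, FN = 4. Check: 9/36 = 0.25, 9/13 = 0.69, 127/131 = 0.97, 127/154 = 0.82.

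**Step 2. Posterior content as printed.** Content = F(upper) − F(lower) = 0.025 − 0.025 = 0, not 0.95. This holds for any counts. With a lower quantile of 0.025, 95% content requires an upper quantile of 0.025 + 0.95 = 0.975.

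**Step 3. Preliminary counts put through both versions**

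| | As printed | With 0.975 |
|---|---|---|
| Precision, Beta(9.5, 27.5) | [0.132, 0.132] | [0.132, 0.407] |
| Recall, Beta(9.5, 4.5) | [0.423, 0.423] | [0.423, 0.886] |

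**Step 4. Confirmatory sample, outburst precision and recall replicated exactly (assumption)**

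- TP = 0.69 × 30.08 = 20.76; FN = 30.08 − 20.76 = 9.32.
- Predicted positives = 20.76/0.25 = 83.02; FP = 83.02 − 20.76 = 62.27.
- TN = 300.79 − 30.08 − 62.27 = 208.44.

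| | As printed | With 0.975 | Preliminary value |
|---|---|---|---|
| Precision, outburst | [0.166, 0.166] | [0.166, 0.351] | 0.25 |
| Recall, outburst | [0.513, 0.513] | [0.513, 0.832] | 0.69 |
| Precision, non-outburst | [0.924, 0.924] | [0.924, 0.978] | 0.97 |
| Recall, non-outburst | [0.717, 0.717] | [0.717, 0.817] | 0.82 |

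The article prints no formula for the non-outburst rows; they use the same form with the classes swapped. All four printed upper bounds lie below the preliminary values, so trigger 2 would fire on every metric. For non-outburst recall this is not due to the quantile alone. Holding outburst precision and recall fixed at 10% prevalence, against 13/167 = 7.8% in Table 4, implies a non-outburst recall of 208.44/270.71 = 0.77, and the corrected upper limit of 0.817 is also just below 0.82.

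**Step 5. Trigger 2 under sampling variation.** The probability that the upper bound falls below the preliminary value, when the true value equals it, was summed from exact binomial probabilities.

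| | Upper quantile 0.025 | Upper quantile 0.975 |
|---|---|---|
| Recall (n = 30, true 0.69) | 0.977 | 0.023 |
| Precision (84 predicted positives, true 0.25) | 0.968 | 0.025 |

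**Step 6. Trigger 3.** As printed the width is always 0, so a width above 0.5 cannot occur. With the correct formula, the widest possible recall interval over all values of TP is 0.344 at 30 outbursts and 0.496 at 13.

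**Step 7. Sensitivity to the counts.** If prevalence were that of the held-out set, giving about 23 outbursts (TP = 16, FN = 7, FP = 48), the corrected intervals would be about [0.157, 0.366] for precision and [0.493, 0.852] for recall. The zero width as printed does not change.

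**The case against.** The strongest reply is that nobody would be misled. The text names the level, gives the posterior distributions, expects different left and right endpoints, and speaks of an upper bound and a width. Given 95% and a lower quantile of 0.025, the upper quantile can only be 0.975. No second plausible analysis is opened, and an analyst is unlikely to report a zero-width interval. This is fair: it shows that the error is almost certainly a slip and that the remedy is not in doubt. It does not make the registered formula right.

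Three narrower points also stand:

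- Trigger 3 would not fire for outburst recall or precision at the planned size under the correct formula either (step 6), so the error makes no practical difference there.
- Trigger 2 firing on every metric describes exact replication. Under sampling variation, almost always is the accurate description for outburst precision and recall. The triggers belong to optional exploratory diagnostics, so a false alarm would prompt extra work and leave the confirmatory estimate unchanged.
- The full stop between the shape parameters has no analytic effect and may come from typesetting or text extraction. The repeated 0.025 cannot easily be explained that way, because it occurs in two separate formulas that are otherwise complete.

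**Conclusion.** The concern holds. As registered, each 95% interval is a single point at the lower 2.5% quantile with 0% posterior content. This follows from the printed formula alone and needs no assumption about the data.

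The size of the effect rests on assumed confirmatory counts: 30.08 outbursts and the preliminary precision and recall. On that basis the stated upper limit is 0.513 where it should be 0.832 for recall, and 0.166 where it should be 0.351 for precision. Trigger 2, read literally, goes from a false-alarm rate of roughly 2 to 3% per metric to about 97 to 98% for outburst recall and precision.

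The error is very probably typographical. It still has to be corrected, because it defines the study's only confirmatory inference and feeds pre-specified rules.

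**What to change.** In section 3.3.3, change the second quantile in both formulas and separate the shape parameters with a comma:

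- Precision: [QBeta(0.025, TP+0.5, FP+0.5), QBeta(0.975, TP+0.5, FP+0.5)]
- Recall: [QBeta(0.025, TP+0.5, FN+0.5), QBeta(0.975, TP+0.5, FN+0.5)]

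Because triggers 2 and 3 also cover the non-outburst class, it is sensible to write out those intervals at the same time, with shapes TN+0.5 and FN+0.5 for precision and TN+0.5 and FP+0.5 for recall.

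The cost is an edit to two formulas. The prior, the credible level, the sample size and the data collection are unaffected. The correction should be dated and recorded before the confirmatory data are analysed.

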## 1. Introduction

Irritability and temper outbursts are one of the most common reasons for child mental health referrals [1–3] and are associated with long-term significant functional impairment and mental health problems [1,4]. Irritability is complex; clinically, it is transdiagnostic and presents across numerous diagnoses [5] and is not a unitary construct but rather consists of discrete dimensions [6]: tonic irritability and phasic irritability. Whereas tonic irritability refers to a baseline cranky, grumpy and negative mood, phasic irritability is associated with discrete behavioral manifestations of anger and temper outbursts. Tonic and phasic irritability are known to have differential relations [7] between and specific mood and anxiety disorders, differences in co-morbidity with ADHD [8] and differing genetic associations [9]. Here, we examine different clinical and behavioral features, measured repeatedly, in vivo, to see if differential clinical symptoms can predict temper outbursts.

The use of real-time, *in vivo* metrics using smartphones and other wireless devices provides the possibility of obtaining naturalistically situated information on the psychological state of children with symptoms of irritability across different clinical conditions (i.e., disruptive mood dysregulation disorder (DMDD), oppositional defiant disorder (ODD), sub-threshold symptoms of DMDD (sub-threshold DMDD), attention deficit hyperactivity disorder (ADHD)) by means of digital-based phenotyping using ecological momentary assessment (EMA) [10–12]. EMA data has the potential to provide the clinician with valuable insight into longitudinally presenting dynamics of irritability and other related clinical symptoms [13]. Our goal in this observational work is to test the degree to which dynamic clinical phenotyping via EMA enables the prospective prediction of temper outbursts in a sample enriched for psychopathology.

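### Without an EMA-free comparator, a confirmatory result that meets expectations cannot be attributed to the momentary EMA answers

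*Protocol article*

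**What the plan says.** The Introduction gives the goal as testing how far "dynamic clinical phenotyping via EMA enables the prospective prediction of temper outbursts in a sample enriched for psychopathology", and motivates it by a possible early-warning system.

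The hypothesis in section 3.1 is broader. It names age, sex, feeling states, day of week and time of day together, in one model shared across participants. Section 3.3.1 lists the same kinds of predictors for the pre-fitted model.

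The inference criteria in section 3.3.3 are posterior intervals for precision and recall, using "the uninformative Jeffreys prior" and pooling all confirmatory prompts. The expectations start from a preliminary model that "achieved a precision of 0.25 and recall of 0.69 for temper outbursts". For precision, the plan expects that "the 95% posterior credible interval for the precision will contain a left endpoint greater than 0.1", with the upper limit below 0.4. For recall, the interval should "contain a left endpoint greater than 0.55 and a right endpoint less than 0.95".

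Table 2 gives the participant-level outburst frequency (mean, SD, range) as "0.17 (0.21) [0.0, 0.73"] for girls and "0.06 (0.09) [0.0, 0.33"] for boys.

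Section 3.3.4 adds two exploratory parts: a comparison of fine-tuned models with the original model, and diagnostics that run only if results depart from preliminary performance.

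**The concern.** Girls have nearly three times the outburst frequency of boys, and the spread between youths is wide within each sex. Pooled precision and recall reward a model for identifying which youths have outbursts as well as for identifying when they occur. Only the second depends on momentary answers, and only the second serves an early warning.

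No planned analysis separates the two. The individualized models are compared with the original model. The diagnostic triggers compare confirmatory with preliminary performance. The leave-one-out diagnostic removes one variable at a time, runs only if triggered, and never removes the EMA answers as a block. If the results land where the plan expects, nothing further is done, and readers may credit the EMA answers with performance that sex and age could partly supply.

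The fixed precision floor of 0.1 is a related weakness. It equals the outburst rate assumed in section 3.2.3 and does not follow the rate actually observed.

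**Working it through.** **Inputs**
- Prompts: 300.79 from 20 participants, 10% with an outburst (section 3.2.3).
- Girls: 20 of 54, or 37% (Table 1).
- Outburst frequency: 0.17 for girls, 0.06 for boys; overall between-youth SD 0.16 (Table 2).
- Model: precision 0.25, recall 0.69 (Table 4); lag-2 AUC 0.78 (section 2.4.2).
- Intervals: 2.5% and 97.5% quantiles of Beta(TP + 0.5, FP + 0.5) for precision and Beta(TP + 0.5, FN + 0.5) for recall. Section 3.3.3 prints 0.025 for both limits; I take the upper one as 0.975.

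**The plan's own figures**
- Expected outbursts: 300.79 × 0.10 = 30.08, as stated.
- Table 4: TP 9, FP 27, TN 127, FN 4 gives precision 9/36 = 0.25 and recall 9/13 = 0.69, as stated.
- Overall rate from the two sexes: (34 × 0.06 + 20 × 0.17)/54 = 5.44/54 = 0.10, matching Table 2.

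**A rule that uses sex alone: flag every prompt from a girl**
- Flags: 300.79 × 20/54 = 111.4.
- TP = 0.17 × 111.4 = 18.9; FP = 111.4 − 18.9 = 92.5.
- Prompts from boys: 300.79 − 111.4 = 189.4. FN = 0.06 × 189.4 = 11.4; TN = 178.0.

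| Rule, at expected counts | Precision (95% interval) | Recall (95% interval) |
|---|---|---|
| Sex only | 0.17 (0.109 to 0.248) | 0.625 (0.448 to 0.780) |
| Model at preliminary values | 0.25 (0.166 to 0.351) | 0.69 (0.513 to 0.832) |
| Flag every prompt, 10% rate | 0.10 (0.070 to 0.138) | – |
| Flag every prompt, 15% rate | 0.15 (0.113 to 0.194) | – |
| Expected range, section 3.3.3 | limits within 0.1 to 0.4 | limits within 0.55 to 0.95 |

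The model row uses TP = 0.69 × 30.08 = 20.8, FP = 3 × 20.8 = 62.3 and FN = 30.08 − 20.8 = 9.3.

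The sex-only rule meets the precision range and misses the recall range. The model at its own preliminary recall also misses the recall range, so that range does not reliably separate the two.

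**Sensitivity of the sex-only precision interval**
- Rounding of the girls' rate (0.165 to 0.175): lower limit 0.105 to 0.113.
- 30% to 50% girls: lower limit 0.103 to 0.117.
- 400 prompts, the abstract's figure, at 37% girls: 0.116 to 0.237.

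**Chance in a single sample**

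I simulated 20 youths with 15 prompts each, 7 of them girls. The sex-only rule met the precision range in about 62% of samples with independent prompts and 45% with clustering at the Table 2 SDs. It met both ranges in about 7% and 13% respectively. The model at its preliminary values (independent prompts) met precision in about 79%, recall in about 33% and both in about 22%.

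**The 0.1 floor**

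With 20 youths, the standard error of the mean outburst frequency is about 0.16/√20 = 0.036, so an observed rate near 0.15 is plausible. At that rate, flagging every prompt clears the floor with no skill at all.

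**The case against.** Several points on the other side stand.

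- **The hypothesis includes age and sex.** Precision and recall of the full model address section 3.1 directly, and the Introduction defends population-level prediction as a deliberate choice. Using differences between youths is therefore part of the design. Attribution to EMA answers is a further question, but it is the one the Introduction sets.
- **The floor does some work.** A reader might infer that a no-skill rule passes. At the assumed 10% rate it does not: flagging every prompt gives a lower limit of 0.070. The weakness is only that the floor is fixed.
- **A sex-only result would not go unremarked.** Its AUC is (0.625 + 0.658)/2 ≈ 0.64 against 0.78, beyond the 0.05 margin. Its upper limits for outburst precision (0.248 against 0.25) and non-outburst recall (0.713 against 0.82) would also trigger the diagnostics. Those diagnostics are exploratory, however, and do not test the EMA answers as a group.
- **The sex-only rule is not the model under test.** In Table 5 the female coefficient is 0.17, while the absolute coefficients of the lagged EMA items sum to 1.84. A reader might infer that the model's performance comes entirely from stable differences between youths. Nothing in the document shows that, and the gap between 0.64 and 0.78 leaves room for an EMA contribution.

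What remains is that the plan never measures that contribution.

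**Conclusion.** The point holds as a limit on attribution. As written, the confirmatory analysis can support the full predictor set but cannot show that the momentary answers add to age, sex, day and time.

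A rule using no EMA answer meets the precision range at the plan's expected counts, though only just (lower limit 0.109 against 0.1), and in roughly half of simulated samples (45% to 62%). It would be wrong to conclude that sex alone satisfies the whole set of expectations, since its recall interval falls short. Nor does the plan lack any reference value: the 0.1 floor serves as one while the outburst rate stays near 10%.

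The figures assume equal prompts per youth, and that the preliminary share of girls and outburst rates carry over. The intervals follow the plan in treating prompts as independent.

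**What to change.** Keep the registered precision and recall analysis unchanged. Before the confirmatory data are opened:

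1. Fit a logistic model with age, sex, day and time only on the same training set, and fix its coefficients.
2. Score it on the same confirmatory prompts as the full model. Report the paired AUC difference (full minus benchmark) with a bootstrap interval that resamples participants, as a pre-specified secondary analysis.
3. State that any claim that EMA answers predict outbursts rests on that difference.
4. Compare precision with the outburst rate observed in the confirmatory set instead of the fixed 0.1.
5. Optionally, report within-participant AUC descriptively, among youths with both outcomes.

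No new data are needed, and the extra analysis is small. The cost is in precision: with about 20 youths and 30 outbursts the difference will be estimated imprecisely, and the claim about EMA answers may come out weaker than the raw precision and recall suggest.
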